### 2.3.5 Adverse Events

Space will be provided in the CRF specifically for recording observed and reported adverse events. All unwanted effects, whether considered to be caused by the study medication or not, will be reported to Thornton & Ross Ltd by completing the Adverse Event form.

### 2.3.6 Serious Adverse Events

If the adverse event is serious, it shall be reported immediately, by e-mail and telephone and by facsimile to the Medical Contact and Thornton & Ross Ltd. A full written report will be forwarded to Thornton & Ross Ltd, by facsimile, within 3 working days.

Serious adverse events are defined as events that are fatal, life threatening, disabling or incapacitating, cause or prolong hospitalisation, overdose (of any kind, with or without symptoms), newly diagnosed cancer or clinically abnormal laboratory values (with or without symptoms).

The contacts for all serious adverse events are:

| **Study Sponsor contact**:  [name]  Pharmacovigilance and Medical Information Department  Thornton & Ross Ltd  [name]  [contact] - Direct line with voicemail.  [name] - Main switchboard.  [contact] - Address to “Pharmacovigilance and Medical Information Department” and mark as **Urgent**  E: [[contact]](mailto:[contact]) or [[contact]](mailto:[contact]) |
| --- |
| **Local Medical contact**:  [name]  Oakfield Surgery,  [name]  [contact]  [contact] |

### 2.3.7 Withdrawals

Participants may be withdrawn from the study at any time for the following reasons:

Adverse Event:

The participant is withdrawn from the study by the Investigator because of an adverse event, whether or not the Investigator believes it to be serious or caused by the study medication, and provided that the Investigator considers it is in the participant's best interest to be withdrawn. There must be a corresponding entry on the Adverse Events and/or the Serious Adverse Events Form in this instance.

Non-compliance:

The participant is withdrawn because of failure to comply with the treatment regimen, or comply with the investigations as required, but is still accessible to the Investigator.

Drop Out:

The participant withdraws consent to continue in the study, but the Investigator would otherwise consider it appropriate for him/her to continue. The participant remains accessible to the Investigator.

Lost to Follow-up:

The participant, without explanation, fails to keep appointments as scheduled for study assessments and is not seen again despite the Investigator's effort (letter, telephone, home visit etc.) to re-establish contact.

Death:

All deaths will be treated as Serious Adverse Events and Thornton & Ross Ltd must be informed within 24 hours. All associated documentation must be completed within 3 working days. Full details will be required including a post-mortem examination if possible.

Lack of Efficacy:

The participant elects to withdraw, because the medication is not adequately effective.

# 3. Analysis and Reports

## 3.1 Definition of End Points

### 3.1.1 Safety

Participants will be observed and all untoward effects will be recorded, whether or not they are thought to be related to the study treatment.

Details of the recording of adverse events are shown in section 2.3.5 and 2.3.6.

### 3.1.2 Efficacy

The primary endpoint is cure, indicated by no evidence of active head louse infestation following the second application of treatment, or cure followed by reinfestation, indicated by limited numbers of adult or stage 3 nymphs on Days 9 or 14, as set out in the following treatment outcome algorithm.

The secondary endpoints are to confirm whether the treatment inhibits louse eggs from hatching (as demonstrated by no stage 1 or 2 nymphs after the first treatment) and the safety and acceptability of the treatment regimen.

**Treatment Outcome Algorithm**

This algorithm has been developed by Medical Entomology Centre and P. N. Lee Statistics and Computing Ltd in order to impose limits within which the outcomes of treatment and any lice recovered can be interpreted.

Cure:

No lice present on Day 9 and Day 14.

Re-infestation

The following must all apply:

- - - Lice must be present at Day 9 and/or Day 14.
    - Adult lice and/or stage 3 nymphs must not be present at Days 1, 2 or 6.
    - Stage 1 or 2 nymphs must not be present at Day 9 or Day 14.
    - If stage 3 nymphs are present at Day 9 there must be no stage 1 or 2 nymphs present at Day 6.
    - Stage 3 nymphs may be present at Day 9 or Day 14 although they must not exceed 2* in number.
    - Adult lice should not exceed 2* at either Day 9 or Day 14.

In addition, the following may apply:

- If adult lice are present at Day 9 Stage 1 and stage 2 nymphs may be present at Day 6.

* The number 2 is an interpretation of the limits of “occasional”.

Ovicidal Failure Only

Ovicidal failure is evidenced by the presence of stage 1 nymphs within 2 days of the second treatment administered on Day 7

For ovicidal failure only, specific lice must not be present at Day 9 or Day 14:

- - - At Day 9 there must be no adult lice and no stage 2 or stage 3 nymphs.
    - At Day 14 there must be no adult lice or stage 3 nymphs.

This is equivalent to requiring stage 1 nymphs only at Day 9 and/or stage 1 and/or stage 2 nymphs only at Day 14.

Licidal Failure Only

All other outcomes are licidal failures.

For licidal failure only, there must be no stage 1 nymphs at Day 9 and no stage 1 or stage 2 nymphs at Day 14, so as not to satisfy the condition for ovicidal failure.

Licidal and Ovicidal Failure

Any subject not falling into groups 1, 2, 3 or 4, including those with missing values for the data necessary to make the classification into groups 1-4. This includes any subjects with missing data at days 9 or 14, as well as those subjects with evidence of lice at days 9 or 14, but missing data at days 2 or 6.

.

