Participants will be treated at Day 0 and Day 7 (+/- 1 day). A member of the study team will apply the treatment on both occasions. Participants will be assessed on Days 1, 6, 9 and 14 (+/- 1 day at each assessment) by a different member of the study team. Any lice found at assessments will be taped into the participant’s CRF.

All adverse events will be monitored during the study (see sections 2.3.5 and 2.3.6) and all changes in concomitant illness and medication will be recorded (see section 2.3.4). A Completion/Withdrawal Form will be completed at the end of the study period.

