**2.3.3.6 Assessment Analysis**

Any lice found during the course of the study will be examined under the microscope to establish the sex and/or stage of development of the insects. It is expected that few adult lice will be found during the monitoring period. The presence of small lice (nymphs) will be evidence that not all of the eggs were killed by the first treatment and will be used as a measure of ovicidal activity. Continued monitoring enables the investigation to determine whether the presence of any lice is due to surviving lice or surviving eggs from which nymphs emerge. The occasional adult louse (1 or 2 only) found after the initial infestation is cleared would be indicative of re-infection (see section 3.1.2).

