## 3.3 Proposed Primary and Secondary Analyses

1. To compare efficacy of KindaPed AF (5% 1,2-octanediol alcohol free lotion) with KindaPed (5% octanediol lotion with 20% alcohol) for elimination of infestation by head lice.
2. To compare KindaPed AF (5% 1,2-octanediol alcohol free lotion) with KindaPed (5% octanediol lotion with 20% alcohol) with regard to prevention of louse egg hatching (ovicidal action) by monitoring the presence/absence of juvenile stages of lice following the first and second treatments.
3. To compare KindaPed AF (5% 1,2-octanediol alcohol free lotion) with KindaPed (5% octanediol lotion with 20% alcohol) To investigate 5% 1,2-octanediol alcohol free lotion with regard to participant acceptability.

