## 3.4 Statistical Methods

Sample Size Determination:

The study has been designed to confirm that KindaPed AF (5% 1,2-octanediol alcohol free lotion) has an essentially similar efficacy comparable to that of KindaPed lotion (5% 1,2-octanediol with 20% alcohol). It is not designed as a full equivalence study but is designed to be able to identify any significant differences between the treatments in pair wise comparisons.

This study is based upon the same sample size as that used in four previous studies of head louse treatments conducted on behalf of Thornton & Ross Ltd (CTMK06, CTMK08, CTMK09, and CTMK10) for basic comparative purposes and is estimated to provide adequate data for demonstration of effect. The actual sample size of 40 per group makes allowance for dropout. Comparison of the results from this study can be made with the results from those studies with respect to similarities of population demographics, and with previous studies of 1,2-octandiol lotion (CTEP01 and CTEP02) with respect to efficacy outcome and acceptability.

Interim analysis

It is proposed to conduct an interim analysis of treatment outcome only after enrolment and completion of sixty (60) participants (approximately 20 in each group). This analysis will be conducted blind of treatment allocation using outcome data entered into a spreadsheet which would then be overlaid with treatment allocation identified only as “a”, “b”, or “c”. This will enable the Sponsor to identify whether one treatment is performing exceptionally well or exceptionally poorly and allow them to make a decision in good time whether they wish to extend or to curtail any aspect of the study. The results of this analysis will be conveyed to the Sponsor in narrative form only.

Analytical Methods:

The primary endpoint is the frequency of cure tested using the "intention-to-treat" population in comparison with the body of data obtained during previous studies using overnight or 2-2.5 hour application times for the product. Secondary endpoints will be the frequency of ovicidal failure and of reinfestation and the numbers of lice seen at the different assessment times. Other endpoints will be the safety of the product and participant acceptance.

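### Ovicidal failure, a secondary endpoint, has conflicting definitions; a frequency taken from the outcome categories would lose Day 6 hatching and count missing visits as hatching

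*Protocol*

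**What the plan says.** Five places in the protocol bear on egg kill.

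- Section 3.1.2 makes inhibition of hatching a secondary endpoint, "as demonstrated by no stage 1 or 2 nymphs after the first treatment".
- Section 2.3.3.6 takes the same reference point: "The presence of small lice (nymphs) will be evidence that not all of the eggs were killed by the first treatment".
- Section 3.3 (like objective 2 in section 1.3) compares the products "by monitoring the presence/absence of juvenile stages of lice following the first and second treatments", with no restriction on stage.
- The Treatment Outcome Algorithm opens its ovicidal category with "Ovicidal failure is evidenced by the presence of stage 1 nymphs within 2 days of the second treatment administered on Day 7". After listing the lice that must be absent, it adds: "This is equivalent to requiring stage 1 nymphs only at Day 9 and/or stage 1 and/or stage 2 nymphs only at Day 14".
- Section 3.4 sets the analysis: "Secondary endpoints will be the frequency of ovicidal failure and of reinfestation and the numbers of lice seen at the different assessment times". It does not say which definition supplies the frequency.

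Three other rules matter. Cure in the algorithm depends only on Days 9 and 14. Re-infestation tolerates stage 1 and 2 nymphs at Day 6 in some cases. Anyone missing Day 9 or Day 14 data goes to the combined Licidal and Ovicidal Failure category.

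**The concern.** The definitions differ in three respects: the treatment they refer to (first or second), the nymph stage (1 or 2, or 1 only), and the time at which a nymph counts (any time after the first treatment, within 2 days of the second, or up to Day 14). The same lice can therefore give different ovicidal-failure rates, depending on which sentence the analyst follows.

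Objective 2 depends on this choice. Day 6 is the visit nominally just before re-treatment and the clearest view of eggs that survived one application. No algorithm category turns a Day 6 nymph into ovicidal failure. In the other direction, a missed late visit is labelled as ovicidal failure although nothing hatched in anyone's sight. If the definition is settled only after the data are seen, the choice could decide the comparison between the alcohol-free product and the original.

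**Working it through.** The protocol gives no rate, event count or power for ovicidal failure, so there is no figure to reproduce. The check is to trace cases, count patterns and work out the visit windows.

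**1. Cases under each rule** (all other visits clear unless stated)

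| Finding | Section 3.1.2 | Algorithm, 2-day sentence | Algorithm category |
|---|---|---|---|
| Stage 1 or 2 at Day 6 only | failure | no | Cure |
| Stage 1 at Day 6, one or two adults at Day 9 or 14 | failure | no | Re-infestation |
| Stage 1 at Day 9 only | failure | yes | Ovicidal Failure Only |
| Stage 2 at Day 14 only | failure | no | Ovicidal Failure Only |
| Stage 2 at Day 9 only | failure | no | Licidal Failure Only |
| Day 14 missing, no nymph seen | no evidence | no evidence | Licidal and Ovicidal Failure |

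**2. Counting presence/absence patterns.** Take stages 1, 2, 3 and adult as present or absent at Days 1, 6, 9 and 14, with complete data and counts of at most 2. These are counts of patterns, not probabilities.

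- Cure: Days 9 and 14 empty, Days 1 and 6 free, so 2^8 = 256 patterns. Three quarters have a stage 1 or 2 nymph at Day 6: 192.
- Re-infestation: Day 1 has 4 allowed patterns. With no Day 6 nymph, Days 9 and 14 have 4 × 4 − 1 = 15. With Day 6 nymphs (3 patterns) stage 3 is barred at Day 9, leaving 2 × 4 − 1 = 7 each, so 21. Total 4 × (15 + 21) = 144, of which 4 × 21 = 84 have Day 6 nymphs.
- Ovicidal Failure Only: Days 9 and 14 allow 2 × 4 − 1 = 7 patterns, times 256 for Days 1 and 6, giving 1,792. Three of the 7 have no stage 1 nymph at Day 9: 3 × 256 = 768. The 2-day sentence and the rule called equivalent to it therefore differ.

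**3. Windows.** Design in Brief allows 1 day either way for the second treatment (Days 6 to 8) and for each visit.

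- Day 6 visit (Days 5 to 7) relative to the second treatment: 5 − 8 = −3 to 7 − 6 = +1 days.
- Day 9 visit (Days 8 to 10): 8 − 8 = 0 to 10 − 6 = 4 days after.
- Day 14 visit (Days 13 to 15): 13 − 8 = 5 to 15 − 6 = 9 days after.

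Of the 9 day combinations for the second treatment and the Day 9 visit, 3 give a gap above 2 days (3, 3 and 4). Of the 9 for the Day 6 visit, 1 puts it after the second treatment.

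**4. Illustration with assumed rates.** With 40 per group, suppose 5% have nymphs that the algorithm counts at Day 9 or 14, and a separate share q have Day 6 nymphs later cleared. Section 3.1.2 counts 40 × (q + 0.05); the algorithm counts 40 × 0.05 = 2.

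| q | Section 3.1.2 | Algorithm |
|---|---|---|
| 10% | 6 | 2 |
| 25% | 12 | 2 |
| 50% | 22 | 2 |

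**The case against.** The best defence is that the protocol has two measures: hatching inhibition in section 3.1.2, and a set of mutually exclusive reasons for failure in the algorithm. On that reading Day 6 data are not ignored. Section 3.1.2 covers them, section 3.3 covers both treatments, and lice counts by visit are a secondary endpoint. This narrows the point but does not remove it. Ovicidal failure is defined by that name only in the algorithm, so the natural reading of section 3.4 is a frequency of algorithm categories, and nothing there says otherwise.

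The 2-day sentence can be called loose wording, because the Day 9 and Day 14 rule is used again under Licidal Failure Only. That is largely fair; the sentence should simply go. Reading it as 2 days either side of Day 7, so as to include Day 6, does not help, because the sentence on equivalence names only Days 9 and 14.

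Treating missing late visits as failure is a reasonable worst case for cure, and some withdrawals may be for lack of efficacy (section 2.3.7). Merely dropping these participants from the numerator would silently count them as egg kill. The denominator has to be fixed too.

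A reader might infer three stronger things that the document does not support:

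- That Cure is wrong for a participant with Day 6 nymphs. The primary endpoint is assessed after the second application, so Cure is correct.
- That ovicidal failure is the leading secondary endpoint. The protocol ranks none.
- That most participants with lice become ovicidal failures because the missing-data rule names Day 2, when no visit is scheduled. The Day 1 visit may fall on Day 2 within its window.

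The most extreme visit gaps (Day 6 visit after re-treatment, Day 9 visit 0 or 4 days after it) need treatment and visit both off by a day in opposite directions. A 3-day gap needs only one of them off by a day. No frequency is known for either.

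**Conclusion.** The point holds as an inconsistency in a secondary endpoint. It leaves the primary cure rule untouched. Sections 2.3.3.6 and 3.1.2 refer to the first treatment and the algorithm to the second. The algorithm's two statements of its own rule are not equivalent, and section 3.4 does not choose between them. If the frequency comes from the categories, first-treatment hatching that later clears is lost under Cure and some Re-infestation cases, and missing Day 9 or 14 data are added as hatching.

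The size in this trial cannot be known from the protocol. The gap of 6 to 22 against 2 in a group of 40 rests entirely on assumed rates, and the pattern counts weight every pattern equally. Day 6 is the clear case, since a nymph at Day 1 could be a survivor and not newly hatched. A separate analysis plan might name one definition, but the conflict stands in the protocol's own text.

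**What to change.** Keep the algorithm for cure. Derive ovicidal failure as a separate yes/no variable, independent of the outcome category, in two parts:

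- **After the first treatment:** any stage 1 or 2 nymph at the Day 6 assessment, where that assessment was made before the second application.
- **After the second treatment:** a stage 1 nymph at the Day 9 visit, or a stage 1 or 2 nymph at the Day 14 visit, or both. Delete the 2-day sentence and use the recorded interval since the second treatment.

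Report both parts for all pairwise comparisons, since objective 2 covers both treatments. Treat missing assessments as missing for this endpoint: an observed-data denominator, with a worst-case sensitivity analysis. Align sections 2.3.3.6, 3.1.2, 3.3 and 3.4 and the algorithm with this wording.

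The treatment and visit windows must also be reconciled. Design in Brief gives the second treatment a window, while section 1.1, the Day 7 treatment section and the algorithm state Day 7 without one, and on paper the order of the Day 6 visit and the second treatment is not secured.

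The cost is wording plus a little extra programming and reporting. Lice found at each visit are already kept and staged under the microscope.

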###### Appendices

Appendix 1 Declaration of Helsinki.

Appendix 2 European (CPMP) Guidelines on Good Clinical Practice for Trials on Medicinal Products.

# Introduction

## 1.1 Summary of the Study

Title: A randomized, assessor blinded, clinical trial to confirm the efficacy of a CE marked class I Medical Device formulation in the treatment of head lice

**Chief Investigator:** [name]

**Estimated Study Start:** September 2010

**Estimated Study Finish:** January 2011

**Participants:** One hundred and twenty (120) evaluable participants will be recruited to the study, randomised between three groups and treated with two vairants of the same CE marked product 5% 1,2-octanediol lotions.

**Type:** Children (aged 6 months and over) and adults who, upon inspection, are found to have live head lice.

**Products:** KindaPed AF (5% 1,2-octanediol alcohol free lotion)

KindaPed (5% 1,2-octanediol lotion with 20% alcohol).

**Methods of Application:** KindaPed AF 5% 1,2-octanediol alcohol free lotion (2-2.5 hours) and KindaPed 5% 1,2-octanediol lotion: These products will be applied directly to dry hair. Sufficient product will be applied to saturate the hair and scalp. The product will be left in place for 2 hours (maximum 2.5 hours) before being removed with proprietary shampoo. The product will be reapplied at Day 7.

KindaPed AF 5% 1,2-octanediol alcohol free lotion (8 hours or overnight): This product will be applied directly to dry hair. Sufficient product will be applied to saturate the hair and scalp. The product will be left in place for a minimum of 8 hours, or left on overnight, before being removed with proprietary shampoo. The product will be reapplied at Day 7.

**Study Design:** This is a randomised, assessor blind clinical investigation designed to confirm efficacy in use and obtain further information about routine usage of two variants of the same CE marked class I Medical Device product with the same active principle in the control and elimination of head louse infestation.

Participants will be assessed at Day 0 (recruitment) and then treated. An investigator will apply the treatment. The same treatment will be reapplied on Day 7.

Participants will be assessed for the presence of live head lice on Days 1, 6, 9 and 14 (+/- 1 day). The assessors will be blind to the treatment group. Any lice found at assessments will be taped into the Case Record Form (CRF) for size analysis.

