2.3.3.3 Follow up Assessments (Days 1, 6 and 9)

Assessments will take place on Days 1, 6, and 9 (+/- 1 day) – see section 2.3.3.5 for Day 14. At assessments, the participant’s hair will be combed with a head louse detection comb, and any lice found will be taped (with clear cellulose tape) into the participant’s CRF. In order to provide blinding and to minimise bias the study team member that conducts the follow up assessments will be different from the team member that applied the treatment at Day 0 and 7.

All adverse events and changes in concomitant medication will be recorded in the CRF.

- - - 1. Follow up Treatment (Day 7)

Treatment will be reapplied at Day 7 following the same procedure as at Day 0 (see section 2.3.3.2).

- - - 1. Final Assessment (Day 14)

The final assessment will take place 14 days (+/- 1 day) after the first treatment (the 15^th^ day of the study). The participant’s hair will be combed with a head louse detection comb and any lice found will be taped (with clear tape) into the participant’s CRF.

Participants who still have live lice at the end of the study will be offered a standard of care treatment (Hedrin 4% liquid gel).

All adverse events and changes in concomitant medication will be recorded in the CRF.

At the Day 14 assessment, the participant and/or parent/guardian will be asked to complete a questionnaire on the treatment that was applied at Day 0. This will include questions on how the participant’s scalp felt, how the hair felt, how easily the product washed out, and how convenient the participant and/or parent/guardian considered this treatment application time.

The Completion/Withdrawal Form will then be completed.

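### The outcome algorithm tests a Day 2 assessment that the schedule does not contain, so a re-infestation can score as success or failure depending on the day of the first follow-up visit

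*Protocol*

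**What the plan says.** The schedule is given three times and is consistent. Section 1.1: "Participants will be assessed for the presence of live head lice on Days 1, 6, 9 and 14 (+/- 1 day". Design in Brief: "Participants will be assessed on Days 1, 6, 9 and 14 (+/- 1 day at each assessment". Section 2.3.3.3: "Assessments will take place on Days 1, 6, and 9 (+/- 1 day", with Day 14 covered separately in the section on the final assessment. None of them names a Day 2 visit.

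The Treatment Outcome Algorithm in section 3.1.2 names Day 2 twice:

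- One criterion for re-infestation is "Adult lice and/or stage 3 nymphs must not be present at Days 1, 2 or 6".
- The last category, licidal and ovicidal failure, is a residual. It takes in participants who fit no other group, "including those with missing values for the data necessary to make the classification into groups 1-4". It then gives particular cases, among them "those subjects with evidence of lice at days 9 or 14, but missing data at days 2 or 6".

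Section 3.1.2 makes the primary endpoint cure, "or cure followed by reinfestation, indicated by limited numbers of adult or stage 3 nymphs on Days 9 or 14", and refers to the algorithm for the details. A re-infestation is therefore a success, and the other outcomes with lice at Day 9 or 14 are failures. Section 3.4 lists the frequencies of ovicidal failure and of reinfestation as secondary endpoints. It also plans an interim analysis of treatment outcome once 60 participants have completed.

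**The concern.** The algorithm decides who counts as a primary success, and it does so partly on a day when no visit is due. A participant assessed on Day 1 has no Day 2 record. If that gap is taken as missing data, lice at Day 9 or 14 lead straight to licidal and ovicidal failure, whatever their number and stage.

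Two analysts could score the same case record forms differently and each could point to the protocol. Because the protocol fixes this rule itself, it is not a detail left to a later analysis plan. If the reading is chosen only when outcomes are being classified, it may be chosen with results in view. The first such occasion is the interim analysis, after which the sponsor may extend or curtail the study.

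**Working it through.** **Inputs.** Visit days and window: section 1.1, Design in Brief and section 2.3.3.3. Classification rules: Treatment Outcome Algorithm. Success definition: section 3.1.2. Group size of 40: section 3.4. The protocol states no figure on this point, so there is none to reproduce.

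**Step 1: days side by side.**

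| Place | Days named |
|---|---|
| Schedule | 1, 6, 9, 14 |
| Re-infestation criterion, early days | 1, 2, 6 |
| Explicit missing-data sentence, early days | 2, 6 |

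Day 2 is tested but not scheduled. Day 1 is scheduled but absent from the explicit missing-data sentence.

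**Step 2: one participant, two dates.** Take a participant with no lice at the first follow-up visit, Day 6 or Day 9, and one adult louse at Day 14. All re-infestation criteria on lice are met. Apply the explicit missing-data sentence as written:

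- First visit on Day 1: there is no Day 2 record, so the class is licidal and ovicidal failure, a primary failure.
- First visit on Day 2 (Day 1 plus one day): a Day 2 record exists, so the class can be re-infestation, a primary success.

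**Step 3: which categories can be reached.** Enumerate the possible findings with every scheduled visit attended.

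- Early findings: adults or stage 3 nymphs at the first visit (yes/no), the same at Day 6 (yes/no), stage 1 or 2 nymphs at Day 6 (yes/no): 2 × 2 × 2 = 8.
- Day 9: 0–3 adults, 0–3 stage 3 nymphs, stage 2 (yes/no), stage 1 (yes/no): 4 × 4 × 2 × 2 = 64. Day 14: likewise 64.
- Total: 8 × 64 × 64 = 32,768 patterns.

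Counts when the early visit is recognised:

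- Cure (no lice at Day 9 or 14): 8.
- Re-infestation: no early adults or stage 3 nymphs, no stage 1 or 2 nymphs at Day 9 or 14, and at most 2 adults and 2 stage 3 nymphs at each. With no stage 1 or 2 nymphs at Day 6, 9 × 9 − 1 = 80. With them, stage 3 nymphs at Day 9 are barred, so 3 × 9 − 1 = 26. Total 106.
- Ovicidal failure only: stage 1 only at Day 9 (2 options), stage 1 and/or 2 only at Day 14 (4 options), less the louse-free pattern: 8 × (2 × 4 − 1) = 56.
- Licidal failure only: no stage 1 at Day 9 and no stage 1 or 2 at Day 14, less cure and re-infestation: 8 × 32 × 16 − 8 − 106 = 3,982.
- Licidal and ovicidal failure: 32,768 − 8 − 106 − 56 − 3,982 = 28,616.

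| Reading | Cure | Re-infestation | Ovicidal only | Licidal only | Both |
|---|---|---|---|---|---|
| Literal, first visit on Day 1 | 8 | 0 | 0 | 0 | 32,760 |
| Literal, first visit on Day 2 | 8 | 106 | 56 | 3,982 | 28,616 |
| Days 1 and 2 as one early visit | 8 | 106 | 56 | 3,982 | 28,616 |

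These are counts of patterns and not expected frequencies. They show only which categories can be reached.

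**Step 4: size per participant.** One re-infestation recoded as failure in a group of 40: 1/40 = 2.5 percentage points. For an assumed 1 to 6 such participants, the loss is 1/40 to 6/40, or 2.5 to 15 points. The range is illustrative, since the protocol gives no re-infestation rate.

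**The case against.** The best defence is that the last category is a residual. It is limited to data needed for the classification, and the sentence naming Day 2 illustrates that limit. A day on which nobody was due to attend is not naturally missing. On that view Days 1 and 2 are one early visit and all five categories work. This is a sensible reading, but the protocol does not state it. The illustration itself treats Day 2 as needed, and the re-infestation criterion lists Day 2 separately from Day 1.

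Several stronger inferences are tempting, and the documents do not support them:

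- *Re-infestation can never be assigned, and everyone with lice at Day 9 or 14 is misclassified.* The window allows a first visit on Day 2, and then the category is reachable even on the literal reading.
- *Three categories are empty by construction.* That holds only for participants seen on Day 1 and only if the illustrative sentence overrides the category definitions. Ovicidal failure only is defined on Days 9 and 14 alone: "This is equivalent to requiring stage 1 nymphs only at Day 9 and/or stage 1 and/or stage 2 nymphs only at Day 14". Day 2 is not needed for it.
- *A missed Day 1 visit is never treated as missing.* The re-infestation criterion names Day 1, so the general clause on data needed for the classification reaches it. Only the explicit sentence leaves it out.
- *The groups are biased against one another.* The same rule applies to all three groups, and nothing in the protocol shows that the first visit would fall on different days by group.

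**Conclusion.** The point holds as an error in the text of the primary-endpoint definition: the algorithm and the visit schedule do not agree. Read literally, the class of a participant with lice at Day 9 or 14 can turn on whether the first follow-up fell on Day 1 or Day 2, with the louse findings unchanged. Re-infestation is the category that matters most, because its own criteria cite Day 2 and because it alone among the affected categories counts as success.

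The size is 2.5 points per recoded participant in a group of 40. The total depends on a re-infestation rate that the protocol does not give and on which reading the analyst adopts. Under the one-early-visit reading the loss is nil. The correction is still needed, because the text does not choose between the readings.

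**What to change.** In both the re-infestation criterion and the missing-data sentence, replace the references to Day 1 and Day 2 with: the first follow-up visit (Day 1, within its +/- 1 day window) or the Day 6 visit. A missed first follow-up visit then counts as missing, and an unscheduled Day 2 does not.

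Simply writing Day 1 in place of Day 2 would not be enough. Read as literally, it would mark as missing a participant whose first visit fell on Day 2, which the window allows.

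Run the corrected algorithm on a few invented records, including first visits on Day 1 and on Day 2 and a missed first visit, and settle the wording before the interim analysis of treatment outcome. The cost is a short written amendment under section 4.12, with ethics and regulatory approval if it is judged substantive. Visits, data collection and sample size do not change.
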